This is a mixed methods research study including the collection of data from patient's medical notes, interviews and quality of life questionnaires in accordance with the schedule of assessments (SoA, Annex I). This study also involves the implementation of an auditory-visual sensory stimulation package in the cardiac ICU at ICHT to participants enrolled in the study. Digital photos will be shown continuously at the patient bedside after cardiac surgery and will always have reference to time and date. Additionally, videos will be played throughout participants' stay in ICU for at least three times per day and upon participant request. Videos will be also played when participant show signs of ICU delirium with the aim of reducing delirium incidence and improve overall better health outcomes. Simultaneously, primary outcomes measures (CAM-ICU, a routine delirium screening measure) will be collected by the research team, as this is evaluated twice a day as per usual standard of ICU practice, with the aim of assessing whether patients develop delirium during their stay in ICU.

Interviews with patients and families/friends will be held in three different occasions. The first one will be on the same day as ICU discharge, the second interview will be on the day of hospital discharge and the third one will be carried out up to a month following hospital discharge during their clinical follow-up appointment. Where possible, family members/friend and patient's interviews will be conducted together (dyadic interviewing), but the possibility of performing interviews separately will be given, so that participants feel able to discuss opinions freely without influence. Nurses' interviews will be held as a one-off and after they have provided direct care to participants who received the proposed intervention.

Each patient will be followed up daily on the wards and once at the monthly follow-up clinic up after ICU discharge, where cognitive and emotional assessments will be performed to evaluate delirium outcomes. The research team will also collect relevant information from participant's medical notes if any complications post ICU discharge arise during inpatient and follow-up stages.

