## **6. STUDY ASSESSMENTS**

### **6.1. ASSESSMENT AND FOLLOW UP**

#### **STUDY INTERVENTION**

The intervention will require family members/friends (selected by patients) to self-record short videos (during the preoperative stage) based on a carefully drafted guided script divided into two parts: a) Reorientation (discussing date/time/surroundings, family members on the video); b) Reassurance (providing comforting/supportive messages). Videos will be recorded either with a video-recorder device (provided by the research team) in the pre-operative clinic or at home using a personal smartphone. At a later stage, videos will be sent to an encrypted NHS email and securely uploaded in line with ICHT Information Governance to a password-protected iPad, which will also facilitate family-patient video calls in ICU. In addition, patients will be requested to select personal pictures pre-operatively, which will be also sent to the PI's encrypted NHS email and securely uploaded into a special digital photo frame with reference to time and date.

Digital photos will be shown continuously at the patient's bedside for 12 hours a day (between 8am to 8pm) and different family videos will be played three times at specific hours of the day (9am, 2pm and 7pm) throughout their stay in ICU. Additionally, videos will be also played upon patient request and last video shown that day will be re-played. In occasions when patients develop ICU delirium and considering personal consultee's agreement, the last video shown to participants will be re-played and patients will be closely monitored. This will help the research team to understand if the combination of personal pictures and family videos impacted patients' orientation and reassurance and if, ultimately, promoted the reduction of ICU delirium. The PI will be responsible for setting up the required equipment and delivering the intervention alongside ICU nurses as illustrated in the study diagram below (Annex XI).

The draft guided script of reorientation and reassurance messages was initially developed based on published research and considering patients' memories from their lived ICU experience(s) [15]. Subsequently, it was further refined within a lay focus group of patient and public members (with ICU lived experience) and reviewed by an expert panel comprising two critical

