care consultants, two critical care nurses and one clinical academic research nurse (Annex XIII). Family members and friends will be requested to not deviate from the draft script order of events and to frequently mention the patient's name at the beginning/end of sentences when recording the video. They will be also asked to provide personalised messages in the second part of the video and to use simple terms equivalent to a 5th-grade reading level. The research team expects that part A) of the video to be similar between study participants, but part B) tailored to each individual participant.

Additionally, as previously agreed and supported by the critical care nursing lead for the ICU at Hammersmith Hospital, all critical care nurses will contribute to the study by filling in a daily checklist (Annex XII). This checklist will help the research team to understand the impact of the study intervention and if participants developed ICU delirium. Moreover, as per standard ICU practice at ICHT, patients following cardiac surgery will be closely monitored and primary outcomes regularly collected by critical care nurses.

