| 5 | Did the patient look at the digital photo frame during the day?                                     |  Yes  No
If “Yes”, how many times: ____                                                                                                                                                                                     |
| 6 | Did the intervention impact ICU nursing care?                                                       |  Yes  No
If “Yes”, please specify: ____                                                                                                                                                                                     |
| 7 | Was the family intervention delivered without any untoward events (eg., acute distress)?            |  Yes  No
If “No”, please specify: ____                                                                                                                                                                                      |
| 8 | Did the patient request to watch the video more than 3 times a day?                                 |  Yes  No
If “Yes”, please specify the total number of times: ____                                                                                                                                                           |
| 9 | Did the patient develop delirium during the day (8am-8pm)?                                          |  Yes  No
9a. If “Yes”, was the video played again?
 Yes  No
9b. If “Yes”, did it improve delirium status?
 Yes  No |

Table 2. Nursing Checklist Night-time

| N | Nursing Checklist Night-time (8pm – 8am)                          | Tick as appropriate                                                                                                                                                                                                                                                            |

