|----------|-------------------------------------------------------------------|--------------------------------------------------------------------------------------------------------------------------------------------------------------------------------------------------------------------------------------------------------------------------------|
| 1 | Were any visual/auditory aids removed prior to sleep?             |  Yes  No                                                                                                                                                                                                                       |
| 2 | From a nurse’s perspective, how many hours did the patient sleep? | _____ hours                                                                                                                                                                                                                                                                    |
| 3 | Did the patient request to watch the video overnight?             |  Yes  No
If “Yes”, how many times: ____                                                                                                                                                                                     |
| 4 | Did the patient develop delirium overnight?                       |  Yes  No
4a. If “Yes”, was the video played again?
 Yes  No
4b. If “Yes”, did it improve delirium status?
 Yes  No |
| 5 | Was the iPad plugged in to charge overnight?                      |  Yes  No                                                                                                                                                                                                                       |

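### Checklist items 9b and 4b record response to a video replay only as an ICU nurse's Yes/No opinion, with no replay time, re-test or comparator

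*Protocol*

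**What the plan says.** **Purpose of the checklist.** Section 6.1 (Study Intervention) has critical care nurses complete a daily form and states: "This checklist will help the research team to understand the impact of the study intervention and if participants developed ICU delirium". The same section provides for the last video to be replayed when a patient becomes delirious, with close monitoring. It expects this to help show whether the photos and videos oriented and reassured patients and, in the end, lowered delirium.

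**The form.** Annex XII, Table 1 item 9 asks "Did the patient develop delirium during the day (8am-8pm", and Table 2 item 4 asks "Did the patient develop delirium overnight". Items 9a and 4a ask whether the video was played again. Items 9b and 4b ask "did it improve delirium status". All are Yes/No.

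**Who delivers.** Section 6.1: "The PI will be responsible for setting up the required equipment and delivering the intervention alongside ICU nurses".

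**The named delirium measure.** Section 3: "primary outcomes measures (CAM-ICU, a routine delirium screening measure) will be collected by the research team". The frequency given there is two assessments daily, done in routine care. Section 6.1 adds that critical care nurses collect it, and Annex I schedules CAM-ICU and RASS in ICU from D0 to D3.

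**Replay trigger.** Section 3 ties replay to signs of delirium, Section 4.6 (Patients Regaining Consent) to a diagnosis, and Section 6.1 to delirium developing.

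**The concern.** Items 9b and 4b ask for a causal judgement: did the replay make the delirium better? The form supplies nothing that would support one. It does not say how improvement is assessed, how long after the replay, or against what. The rater knows the video was played and belongs to the staff group delivering it.

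Delirium comes and goes, so some patients will look better after a replay whether or not the video did anything. If the ticks are tallied to address the aim in Section 6.1, the result will look like a response rate but cannot be read as one. The gap also cannot be closed at the analysis stage. Without a replay time, a replay cannot be reliably linked to the CAM-ICU results charted around it.

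**Working it through.** There is no stated figure to reproduce. Section 7 bases the 12 patients on previous feasibility studies, and no power calculation bears on this point. The check is mainly of the text, with some arithmetic for scale.

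**1. What the form captures about a replay.**
- Scheduled videos: Table 1 item 3 has spaces for three clock times.
- Replays for delirium: items 9a and 4a have a tick only, with no time.
- Response: items 9b and 4b have a tick only, with no instrument, interval or repeat CAM-ICU.
- Each table covers a 12-hour period, so several episodes or replays in one period collapse into one answer.

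**2. Whether a comparison exists.** Section 3 gives the package to the participants enrolled, with no control group. On its natural reading, 9b applies only where 9a is Yes, so delirious periods without a replay produce no improvement rating either. Let r be the share of delirious episodes that would be rated improved with no effect of the video, and d the true effect. The expected share of Yes is then r + d, plus any rating bias. One observed proportion cannot separate these terms. The documents give no value for r. As an assumption only, r = 0.30 to 0.50 would produce 30% to 50% Yes when d = 0 and there is no rating bias. The argument does not depend on that range.

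**3. Whether another record covers the replay.** CAM-ICU is charted twice daily, but without a replay time a given result cannot be placed before or after the replay. The ward CAM, MoCA, GAD-7 and PHQ-9 come after ICU discharge. Interviews address the intervention as a whole. Items 9b and 4b are therefore the only structured record of response to a replay.

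**4. Scale.** Inputs: n = 12 (Section 7); delirium 30% to 80% across ICU patients and up to 55% after cardiac surgery (Section 1.1).
- Expected delirious patients: 12 × 0.30 = 3.6; 12 × 0.55 = 6.6, so about 4 to 7.
- Shift in a patient-level improved proportion per tick: 1/4 = 25 points; 1/7 = 14.3 points.
- At the upper ICU figure: 12 × 0.80 = 9.6, about 10 patients, and 1/10 = 10 points.
- Exact (Clopper-Pearson) 95% intervals: 2 of 4 gives 6.8% to 93.2%; 3 of 7 gives 9.9% to 81.6%.

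The denominator is patients who were delirious and had a replay. It may be smaller than the number delirious, and each tick would then count for more.

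**The case against.** A reader might go further and infer that delirium incidence itself depends on which source is used, because items 9 and 4 ask about delirium without citing CAM-ICU. The documents do not support that. Section 1.1 describes CAM-ICU as the tool for diagnosis, Sections 3 and 6.1 collect it to establish whether delirium developed, and Annex I lists only CAM-ICU and RASS for delirium in ICU. Nothing proposes counting a patient as delirious if either source is positive. Nurses from the same group complete both records and may simply copy the result across. Naming CAM-ICU as the source is therefore a clarification.

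Three other readings also go too far:
- *That 9b and 4b are the study's only measure of impact.* The interviews, questionnaires and other checklist items also bear on impact.
- *That the checklist is unstructured.* It is a fixed form; what is missing is any criterion behind these particular items.
- *That the rater is the nurse who replayed the video.* The Protocol says only that ICU nurses deliver alongside the PI.

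It is also fair to say that Section 7 plans no summary or test of 9b and 4b, that a nurse's immediate impression is legitimate feasibility data, and that CAM-ICU is equally unblinded here. With two assessments a day, evenly spaced, the next one could fall up to about 12 hours after a replay. These points stand, and they argue against replacing the nurse's impression with CAM-ICU. They do not answer the narrower point: Section 6.1 looks to the replay and the checklist for evidence of impact, and the form omits what is needed to interpret the answer. Nor can a statistical analysis plan supply times that were never recorded.

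**Conclusion.** The point holds for items 9b and 4b. As designed, they yield an unblinded opinion about cause that cannot be separated from natural fluctuation, although Section 6.1 looks to the replay and the checklist for evidence that the package reduced delirium. With about 4 to 7 delirious patients expected, one tick moves a patient-level proportion by about 14 to 25 points. That range rests on the background rates of 30% to 55% applying to this unit and on all delirious patients having a replay. The qualitative conclusion needs neither assumption.

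Severity is low to moderate. The primary objective is feasibility and acceptability, delirium incidence is secondary, and its natural source, CAM-ICU, is already identifiable. The change should be made before data collection, because missing replay times may not be recoverable.

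**What to change.** 1. **Annex XII, items 9a and 4a:** add the clock time of each replay, the last charted CAM-ICU/RASS result before it, and the next scheduled result after it, each with its time.
2. **Items 9b and 4b:** keep them, labelled as the nurse's perception. Report them and the paired CAM-ICU/RASS results descriptively, not as improvement caused by the video.
3. **Section 6.1:** add a sentence stating that delirium incidence is taken from charted CAM-ICU, and that items 9 and 4 serve to log delivery and to describe agreement with CAM-ICU.
4. **Replay trigger:** reconcile the wording in Sections 3, 4.6 and 6.1, so that what counts as an occasion for replay is the same throughout.

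The cost is two more lines on the form and a few sentences of text. No assessment is added, since for CAM-ICU "this is evaluated twice a day as per usual standard of ICU practice". The limitation remains that the next CAM-ICU is unblinded and may fall hours after the replay, so the paired results describe what followed a replay and do not show that it worked.

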### INPATIENT AND FOLLOW-UP STAGES

Whilst patients remain in ICU, clinical data will be collected from medical records by the PI with the aim of assessing if ICU delirium was developed during this period. Such clinical data is documented and measured routinely as per the standard of care and it includes:

- Relevant medical history
- Relevant intra-op complications
- Vital signs and primary outcomes (e.g., CAM-ICU measurements)
- New prescriptions (associated with prevention/management of ICU delirium)
- Relevant post-operative complications

Subsequently to ICU discharge, each patient will be followed up daily on the wards and one time after hospital discharge at the standard of care monthly follow-up clinic. During this stage, the PI will perform different quality of life questionnaires, such as cognitive and emotional assessments as recommended by the international community when evaluating delirium outcomes in hospital settings [17]. Cognitive and emotional assessments will be performed according to the SoA below and will include the use of the following tools:

- CAM (Confusion Assessment Method)
- Montreal Cognitive Assessment (Annex XVII)
- Generalised Anxiety Disorder Assessment-7 (Annex XVIII)
- Patient Health Questionnaire-9 (Annex XIX).

Any relevant clinical complication that might arise during the follow-up period, will be also collected by the PI and further discussed with the CI and SI.

### INTERVIEWS

The interviews will be made in accordance with the study participants' schedule and will run for approximately 20 minutes.

Two dyadic interviews with patients and family members/friends will take place at the hospital during the inpatient stay time: the first will be held on the day of ICU discharge and the second on the day of hospital discharge. The third interview will happen at the post-operative follow-

up appointment or virtually (depending on participants' preference) one month after hospital discharge. Where possible, family members/friends and patients interviews will be conducted together, but the possibility of performing interviews separately will be given, so that participants feel able to discuss opinions freely without influence. Interviews directed to healthcare professionals will take place either virtually or in private rooms located in ICU, considering physicians' availability and preferences. In such circumstances, researchers will follow local Trust guidance on the use of personal protective equipment and social distancing. All interviews will be conducted by the PI. They will be audio-recorded and transcribed by the PI and the research supervisors. An ICHT encrypted recorder will be used for this process. All data will be anonymised and stored according to the ICHT guidance.

## **6.2. END OF STUDY**

The end of the study is defined as the last subject study visit, including follow-up period. Data from this study will be kept confidential at all times. Only staff on the delegation log will have access to the study data. No identifiable data will be published or made public during this study. The Sponsor (ICHT) will store identifiable information and study documentation about the participants for a minimum of 10 years after the completion of the study.

## **7. STATISTICS AND DATA ANALYSIS**

The study sample size was based on sample size based on previous feasibility studies and complexity of the planned intervention [18]. Considering the study design and timelines, the recruitment target for this study is 12 patients alongside 12 family members. The research team also plans to recruit 6 critical care nurses to be able to collect more in-depth data about the study intervention acceptance in ICU.

**Quantitative data** will be analysed using SPSS statistical software. Descriptive statistics will be used to present demographic data, medical characteristics and causal beliefs about ICU delirium. Correlations will be used to examine the relationships between vital signs, new ICU prescriptions, ICU complications, mortality rates and delirium status. Logistic regression analyses will be applied when investigating the influence of sociodemographic and clinical factors on the identification of patients with ICU delirium.

**Qualitative data** from interviews will be audio-recorded, transcribed verbatim and managed in NVIVO. Framework analysis will be used to systematically manage and holistically interpret qualitative data collected from the interviews. The academic supervisors, [name], [name] and the CI, [name], will be involved in reviewing transcripts, developing the coding frame and identifying potential themes for subsequent exploration. Additionally, the PI will compare concepts from existing literature with those emerging from this study. After identifying the initial themes, the lead researcher will also liaise with a patient and public involvement (PPI) advisory group to check the credibility and usefulness of the selected themes and findings.

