## **1. INTRODUCTION**

Delirium can affect over 50% of patients following cardiac surgery in intensive care units (ICU), leading to long-term cognitive impairment, prolonged hospital stays and increased costs to the NHS. Nurse-led auditory-visual stimulation to help prevent and manage ICU delirium is a relatively novel and unexplored clinical practice in the postoperative cardiac field.

This study aims to assess the feasibility of an innovative intervention using family focused sensory stimulation to reduce delirium in ICU patients following major cardiac surgery and improve post-surgical outcomes.

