### **1.1. BACKGROUND**

Delirium is a common and often undiagnosed brain dysfunction that occurs in ICU and is associated with increased morbidity and mortality [1,2]. Its incidence can vary between 30-80% depending on various risk factors, doubling the National Health Service (NHS) inpatient cost per patient compared to those without delirium [3,4]. It is a complex, distressing and debilitating condition that impacts patients, family members and healthcare professional [5].

Patients undergoing cardiac surgery are a particularly vulnerable group as ICU delirium affects up to 55% of these patients, due to operative reasons including surgical complexity and cardiac bypass time [6,7]. Delirium is associated with increased anxiety and depression, poor functional status, increased risk of stroke and significant cognitive impairment up to a year post-cardiac surgery. It has also been linked with an elevated number of hospital readmissions, longer ICU and hospital lengths of stay [8,9].

Given the significant burden on patients and the NHS, delirium prevention and management is considered to be national priority in ICU by the James Lind Alliance [10]. Delirium is potentially preventable and healthcare professionals must diagnose this condition in critical care units by using the Confusion Assessment Method (CAM-ICU) screening tool as per the UK National Institute for Health and Care Excellence (NICE) guidelines [11,12]. Whilst pharmacological interventions are the mainstay of treatment in ICU, the Society of Critical Care Medicine highlights the importance of non-pharmacological therapies in the management of ICU delirium [2]. Therefore, there is an urgent unmet need to identify novel non-pharmacological management strategies to prevent and treat ICU delirium [10].

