## **3. STUDY DESIGN**

The study will be conducted over twelve months in the Cardiac Intensive Care Unit at Hammersmith Hospital, Imperial College Healthcare NHS Trust. For this study, a total of 30 individuals (12 patients, 12 family members or close friends and 6 critical care nurses) will be recruited and interviewed to allow sufficient depth and richness of data. Patients and family members/friends will be mainly recruited from the ICHT pre-operative clinic outpatient department, which runs several pre-operative clinics per week. Each week, approximately eight patients undergo cardiac surgery, and the research team intends to recruit one patient and their family member/friend per a week for a period of 4 months.

All participants will be given time to consider their participation in the study and if happy will be consented by PI or other delegated member of the research team. Patients will be approached during one of their pre-operative clinic appointments and informed consent will be sought at this stage. Once written consent has been obtained, patients will be asked to nominate a family member or friend to be contacted by the PI. After signing the consent form, family members/friends will also be enrolled into the study and requested to self-record short videos pre-operatively (based on a guided script - ANNEX XIII), which will be safely uploaded to an iPad. In addition, patients will be requested to select multiple pictures, which will be securely uploaded into a digital photo frame. This package combination of videos and pictures will be shown to patients post-operatively in ICU. Critical care nurses will be recruited after they have provided direct care to at least one participant, who received the study intervention in ICU.

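### Section 7 commits to logistic regression and correlations on delirium in at most 12 patients (about 4 to 7 cases), which cannot give informative estimates; part of the prescription correlation is also circular

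*Protocol*

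**What the plan says.** Section 7 sets the size of the study by precedent: "The study sample size was based on sample size based on previous feasibility studies and complexity of the planned intervention". It continues: "the recruitment target for this study is 12 patients alongside 12 family members". Six nurses are added, but only the patients have a delirium status.

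The same section then fixes two association analyses. The first is: "Correlations will be used to examine the relationships between vital signs, new ICU prescriptions, ICU complications, mortality rates and delirium status". The second is: "Logistic regression analyses will be applied when investigating the influence of sociodemographic and clinical factors on the identification of patients with ICU delirium". Neither is called exploratory. The number of predictors is not limited, and sparse data are not foreseen. Descriptive statistics are planned alongside.

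Section 6.1 (inpatient and follow-up stages) lists the clinical data to be taken from the notes. The prescription item reads: "New prescriptions (associated with prevention/management of ICU delirium".

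On how common delirium is, Section 1 says: "Delirium can affect over 50% of patients following cardiac surgery in intensive care units (ICU". Section 1.1 gives 30-80% for ICU patients generally and, for cardiac surgery, says: "ICU delirium affects up to 55% of these patients". The primary objective (Section 2.1) is feasibility and acceptability. Incidence of delirium is a secondary objective (Section 2.2).

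**The concern.** The method and the sample size are fixed in the same section and do not fit each other. Logistic regression depends on the smaller of the two outcome groups, and with 12 patients that group will hold only a handful. Two results are then likely. Either the fit separates and the software prints an arbitrarily large odds ratio, or it converges with an interval so wide that any statement about influence is unsupported. No later analysis plan can repair this while the method and the 12 patients both stand.

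Two of the correlations have further problems. The prescription variable is restricted to drugs linked to delirium, so where a drug was started because delirium was diagnosed, its association with delirium reflects the definition. Mortality has no variation if nobody dies, and a correlation with a constant is undefined.

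At stake is the credibility of whatever the report says about factors related to delirium, and its use in designing a later trial.

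**Working it through.** **The plan's own figure.** There is no power or precision calculation to reproduce; 12 rests on precedent, complexity and timelines. Section 3 intends to "recruit one patient and their family member/friend per a week for a period of 4 months". That is about 4 × 52/12 = 17 weekly slots, enough for 12 patients but not for a much larger sample. Twelve is also a maximum for analysis, since Section 4.4 lets a withdrawing participant have their data destroyed.

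**Number of cases** = 12 × rate:
- 30% (lower end of the general ICU range, Section 1.1): 3.6
- 41.8% (55% reduced by the 24% cited in Section 1.2, 0.55 × 0.76): 5.0
- 50% (Section 1): 6.0
- 55% (upper figure for cardiac surgery, Section 1.1): 6.6

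Hence about 4 to 7. The 30-55% span is assembled here from two different statements; the protocol does not give it as a range. At its 80% figure there would be 9.6 cases and only 2.4 non-cases, which is no better.

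**Multivariable logistic regression.** I simulated 12 patients with covariates unrelated to delirium at rates of 30%, 42% and 55% (2,000 datasets per setting). Linear programming tested for complete or quasi-complete separation, in which case no finite maximum-likelihood estimate exists.
- Three covariates (two continuous, one binary at 50%): 20-36%
- Five covariates (three continuous, two binary at 50%): 58-70%
- One continuous covariate alone: about 1-3.5%

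The mix matters: three continuous covariates give 12-22%, and one continuous with two binary covariates gives 31-49%.

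**Single binary predictor, six patients per level.**
- 4/6 v 2/6 delirious: OR = (4 × 4)/(2 × 2) = 4.0. SE of log OR = √(1/4 + 1/2 + 1/2 + 1/4) = 1.225. 95% CI = exp(1.386 ± 1.96 × 1.225) = 0.36 to 44.
- 5/6 v 1/6 delirious: OR = (5 × 5)/(1 × 1) = 25. SE = √(1/5 + 1 + 1 + 1/5) = 1.549. Wald z = 3.219/1.549 = 2.08, p = 0.038. The likelihood-ratio statistic is 5.82, p = 0.016. Fisher's exact two-sided p = 2 × (36 + 1)/924 = 0.080. Three standard tests on one table disagree about 5%, so the large-sample tests cannot be relied on here.

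**Correlations.** With n = 12 there are 10 degrees of freedom. At two-sided 5% (assumed), t = 2.228 and critical |r| = 2.228/√(10 + 2.228²) = 0.576. An observed r of 0.5 has a Fisher-z 95% interval of tanh(0.549 ± 1.96/√9) = -0.10 to 0.83.

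**Prescriptions.** Section 6.1 collects only drugs tied to preventing or managing delirium, and Section 7 relates them to delirium status. A drug started in response to delirium can hardly appear in a patient without it, so that part of the association is built in at any sample size.

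**Mortality.** P(no death in 12) = (1 - q)^12. With q assumed at 1-5% (the protocol gives no rate), this is 0.99^12 = 0.89 down to 0.95^12 = 0.54.

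**What 12 patients can support.** An incidence with an exact (Clopper-Pearson) interval: 6/12 = 50%, 95% CI 21-79%.

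**The case against.** The best defence is that these analyses are ancillary. The endpoint is feasibility and acceptability, and neither it nor the incidence estimate uses the regression or the correlations. That stands. A reader might infer that the study's quantitative output as a whole is spoiled; it is not.

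It can also be said that failure to estimate is not certain. That stands too. The protocol fixes no covariate count, and a model with one continuous predictor nearly always converges. The supportable statement is that multivariable models often fail and simple ones are uninformative.

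The protocol names no alpha and no testing rule, so the critical r describes conventional practice, not a stated criterion. That false risk factors would be published as findings is conjecture.

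On prescriptions, a reader might call the whole correlation circular. The item also covers prevention, and a preventive drug may be given to patients who never become delirious, so the charge is firm only for management drugs. Nor do the documents show that no patient will die; that rests on an assumed rate. It is also tempting to say that causal beliefs about delirium, which Section 7 plans to describe, are never collected. The interview questions are not shown and could cover them.

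Finally, covariate selection and sparse-data methods are often left to an analysis plan, and penalised or univariable exploratory estimates would be an alternative to deletion. But the commitment to these methods is made in the protocol itself, and penalisation does not add information to 4 to 7 cases.

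**Conclusion.** Wrong as written; should-fix. The commitment to model influences on delirium in at most 12 patients cannot yield usable estimates. This rests on the protocol's own target and rates. The separation percentages also depend on the assumed number and type of covariates, the significance threshold on an assumed two-sided 5% level, and the 54-89% chance of an undefined mortality correlation on assumed mortality of 1-5%. The conclusion does not hang on any one of these, because the single-predictor intervals alone show it. The circularity of the prescription correlation is a separate defect, limited to drugs started to manage delirium. It is not a must-fix: the primary endpoint, the incidence, the descriptive summaries and the data collection are untouched, and the text can be corrected at any time before analysis.

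**What to change.** In Section 7, replace the sentences on correlations and logistic regression with:
- a per-patient listing, and descriptive tables by delirium status (counts, median and range);
- exact 95% intervals for proportions, including incidence;
- no p-values, and a statement that no risk-factor or association claim will be made.

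Report delirium-related prescriptions as a description of how delirium was managed, not as a correlate of it. Report deaths as a count.

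The change rewords one paragraph, reduces the analysis work, and alters no data collection, recruitment or timeline. The downside is that exploratory association estimates are given up, and at n = 12 these carry almost no information.
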